### Randomization and blinding

Consecutive CSOs, who contact a center randomized to conduct either individual CRAFT or open group CRAFT, will be offered the intervention within two weeks of an intake interview. The intervention consists of six sessions with 7–10 days between each session (Fig. 1).

**Fig. 1 Fig1:**
[figure not shown]
Cluster-randomization of treatment institutions

Consecutive CSOs, who contact a center randomized to the control condition (self-directed CRAFT), will be offered self-help material, only. After three months, and when the primary outcome has been measured, the CSOs in this intervention format will, however, have the possibility of an individual follow-up session with a therapist to make sure that the CSOs are helping to move on.

As can be seen from the design, the control group consists of CSOs randomized to self-help intervention. The self-help intervention is chosen as control condition instead of either Treatment as usual or waiting list. Treatment as usual was disregarded since the interventions, currently being offered to the CSOs in the participating treatment centers, differ a lot one from the other, ranging from nothing, to brief advice on the phone, psycho-education, or personal support. A waiting list is disregarded as control condition since participants, waiting for an intervention or treatment, do not act ‘naturally’, but simply wait and become worse than they would have outside the study [30], potentially leading to an overestimation of the effectiveness of the experimental condition. Instead, offering self-help material to the control group serves as a minimal intervention and, for some CSOs, it may even be sufficiently helpful. Should that be the case, it would constitute an interesting finding and be added to the overall implementation of CRAFT nationwide.

### Participants

The participants of the study are concerned significant others (CSO) to a person with an AUD. There is no consensus definition on a CSO in the literature, but it could, for example, be a spouse, a daughter, a son, a cousin, a friend or a colleague. The CSO must fulfill the criteria listed below to be included in the study. The therapist, who includes the CSO, estimates whether the CSO fulfills the inclusion and exclusion criteria.

Inclusion criteria (CSO):18 years and olderBeing a CSO to a person with AUD, who is not currently under treatment for an alcohol problemHaving the intention to maintain contact during the next 90 daysHaving had regular contact with the PWAUD for the last 90 days (face-to-face contact for several hours on, at least, a weekly basis) or having the wish to re-establish a regular contact to PWAUDBeing prepared, at least to some extent, to support the problem drinker if he/she chooses to seek treatment

Exclusion criteria (CSO):6.Suffering from dementia or other cognitive disorders7.Not speaking Danish8.Being psychotic or otherwise severely mentally ill9.Have been in treatment for AUD in the last three months10.Being concerned about a person who, according to the CSO, mainly uses illegal substances

### Recruitment

Informative leaflets and posters have been distributed to participating local authorities, who are committed to distribute the leaflets via social services departments, departments for children and adolescents, and to general practitioners. Additionally, we recruit participants through advertisements in local newspapers and via videos and posts on Facebook, linking to the participating alcohol treatment centers’ websites and their Facebook pages. Further, we inform about the project on national websites for counseling about alcohol problems such as www.hope.dk and the national telephone hotline ‘Alkolinjen’.

### Timeline

#### Interventions

##### Individual and group sessions

In this study the sessions are compressed to 6 sessions of one hour for individual CRAFT and two hours for group CRAFT in order to test if a shorter period is just as effective as 12–14 sessions (Fig. 2).

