**Discussion:**

We expect to establish evidence as to whether CRAFT is efficient in a Danish treatment setting and whether CRAFT is most effective at individual, group or self-help material only.

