## Methods

### Design

The study is a cluster randomized controlled trial, carried out in public alcohol treatment facilities. All public alcohol treatment centers in Denmark have been invited to participate in a partnership with the Unit of Clinical Alcohol Research at the University of Southern Denmark. In all, 61 institutions were invited to participate, and 17 institutions agreed to participate in the study. The treatment facilities have been randomized to offer one of the three following CRAFT formats:CRAFT as individual format, consisting of six individual sessions with a therapist and a self-help bookCRAFT in an open group format. The groups start when two CSOs have contacted the treatment facility and will then continuously include new members, consisting of six group sessions with one or two therapists, in addition to the participants also getting a self-help book.Control condition, consisting of CRAFT delivered in a self-directed format and using a self-help book only.

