### Ethics

In view of the fact that the CRAFT intervention has proven highly effective in the US, and since living close to a problem drinker is such a burden to the individual and, finally, because the Danish National Guidelines strongly recommend the implementation of CRAFT, we find it un-ethical and problematical not to offer CRAFT in some form to all the participants, even to the control condition. However, since we expect less effect of the control condition (CRAFT as self-help material), for ethical reasons, the participants in the control group will be offered an individual CRAFT session three month after enrollment. Training significant others in new communication strategies and new ways of acting, in relation to the problem drinker, may lead to increased tension in the family set-up. Domestic violence is already relatively more frequent in families with problem drinking, thus, an increased risk may be anticipated. It is, therefore, highly important to address the risk of domestic violence in therapy. Addressing this risk is mandatory in the interventions and includes developing safety plans together with the CSO. It is, however, important to bear in mind that the risk of abuse and suffering, on the part of the CSOs, is even higher if the problem drinking continues unaddressed. We expect no risks or side-effects for the participants.

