## Discussion

The aim of this study is to investigate whether CSOs assigned to individual CRAFT or group CRAFT would be more able to motivate their drinking relative to enter treatment, compared to CSOs randomly assigned to the control condition (self-directed CRAFT) and, furthermore, to investigate whether six-weeks group CRAFT improves the quality of life and psychological functioning of CSOs significantly more than individual CRAFT and self-directed CRAFT.

We expect to find a higher improvement in the quality of life for the CSOs receiving group CRAFT than the ones receiving individual CRAFT, since the CSOs in the group CRAFT benefit from the dynamics that occur in a group of like-minded individuals. Being part of a group creates a sense of mutual recognition and may lower the feeling of isolation and shame among CSOs [42]. Individual sessions may, however, be easier to attend, offer more flexibility, and may allow the CSO to work more freely with what is perceived to be most important. We would like to study if there is a difference in life quality for the CSOs whose relatives enter treatment and those who do not (self-directed CRAFT). This study is also the first to study group CRAFT in Europe and the first study using open group format. CRAFT in a group format may be a relatively cheaper solution [20]. However, individual sessions may be easier to organize in smaller facilities, if waiting lists are to be avoided. If the self-help material proves to be just as effective as other types of intervention it would be a low-cost intervention and easy to implement nationwide.

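### Two promised conclusions, six sessions against 12–14 and CRAFT being efficient in Denmark, have no comparison arm; a null result should be reported as inconclusive

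*Protocol article*

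**What the plan says.** Three statements set out what the trial will show.

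- **Course length.** The section Individual and group sessions says the sessions are compressed to six "in order to test if a shorter period is just as effective as" 12–14 sessions.
- **Efficiency in Denmark.** Aim 2 in the Abstract, repeated under Aim and hypotheses, asks whether individual, group or self-help CRAFT is efficient in bringing drinkers into treatment. The Abstract's Discussion promises "evidence as to whether CRAFT is efficient in a Danish treatment setting", and the last paragraph of the main Discussion promises evidence of efficacy in Denmark.
- **Self-help against the other formats.** The main Discussion says: "If the self-help material proves to be just as effective as other types of intervention it would be a low-cost intervention", and adds that it would be easy to implement nationally.

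The Design section gives three arms: six individual sessions plus the book; an open group "consisting of six group sessions with one or two therapists", plus the book; and a control "consisting of CRAFT delivered in a self-directed format and using a self-help book only". Usual care and a waiting list are rejected under Randomization and blinding, with reasons. The Ethics section calls it "un-ethical and problematical not to offer CRAFT in some form to all the participants".

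Hypothesis 1 is that individual or group CRAFT is superior to self-directed CRAFT. The Power calculation is for a 20-point difference, 60% against 40%.

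**The concern.** A randomized trial supports conclusions about the contrasts between its arms. The first two statements need contrasts that do not exist here: six sessions against 12–14, and CRAFT against no CRAFT. No analysis plan can supply a missing arm, so this is not a detail that the article has left to another document.

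The third statement needs a different kind of evidence from the one planned. Showing that two formats are about equally effective requires an interval narrow enough to exclude a difference that matters. A superiority test sized for 20 points is not built for that.

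At stake is what may be concluded and passed on to the treatment services. Without a non-CRAFT arm, a treatment-entry rate in any one arm cannot be separated from what would have happened anyway. And if face-to-face CRAFT does not beat the book, the reader needs to know whether the data exclude a worthwhile advantage or merely fail to show one.

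**Working it through.** **Claims against arms**

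| Claim | Contrast needed | Available in the Design section |
|---|---|---|
| Six sessions as good as 12–14 | Six sessions vs 12–14 sessions | No; both session arms have six |
| CRAFT, self-help included, is efficient in Denmark | Each format vs no CRAFT | No; all three arms are CRAFT |
| Individual or group better than self-help | Sessions plus book vs book | Yes |

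An external comparison is weak for the first two claims. The Background gives 62% treatment entry for the full course in a US trial, but the Discussion says the high US engagement rates may not be replicated in Denmark. That US trial also reports 37% entry under Al-Anon/Nar-Anon, which does not aim at treatment entry, while the Power calculation assumes 40% for the self-help arm. The populations differ, so this is only an illustration, but it shows that a rate near 40% without a control says little about whether the book works.

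**The plan's own sample size**

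Inputs (Power calculation): 40% vs 60%, α 5% one-sided, power 90%.

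n = [1.645·√(2·0.5·0.5) + 1.282·√(0.4·0.6 + 0.6·0.4)]² / 0.20² = (1.163 + 0.888)² / 0.04 = 105.2, so 106 per arm.

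This matches the stated 106 and confirms a superiority calculation. It matches without a design effect, although an ICC of 0.05 is stated; that is a separate matter, but clustering is included below.

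**Precision for sessions against book**

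From the article: 135 per arm, two losses of 10%, ICC 0.05, 24 clinics in total. Assumptions: 24/3 = 8 clinics per arm (the article gives no split), equal cluster sizes, and 135 × 0.80 = 108 analysed per arm.

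- Cluster size: 108/8 = 13.5
- Design effect: 1 + 12.5 × 0.05 = 1.625
- Effective n per arm: 108/1.625 = 66.5
- Variance term: 0.4 × 0.6 = 0.24 in each arm

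95% CI half-widths:

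- One face-to-face arm vs book: 1.96·√(2 × 0.24/66.5) = 0.167, about 17 points
- Both face-to-face arms pooled vs book: 1.96·√(0.24/66.5 + 0.24/133) = 0.144, about 14 points
- One arm vs book, ignoring clustering: 1.96·√(2 × 0.24/108) = 0.131, about 13 points

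**Chance of a non-significant result**

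For one arm against the book, one-sided 5%, effective n 66.5:

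- True rates 60% vs 40%: power = Φ[(0.20 × 8.155 − 1.163)/0.693] = Φ(0.675) = 0.75, so about 25% non-significant
- True rates 60% vs 50%: power = Φ[(0.10 × 8.155 − 1.157)/0.700] = Φ(−0.49) = 0.31, so about 69% non-significant (57% if clustering is ignored)

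**What a similarity claim would need**

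The article states no margin, so these margins are illustrations only. With both true rates at 60%, one-sided 5%, power 90%, before clustering:

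- 10 points: (1.645 + 1.282)² × 0.48/0.10² = 411.2, so 412 per arm
- 20 points: (1.645 + 1.282)² × 0.48/0.20² = 102.8, so 103 per arm

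The planned size therefore fits a margin of about 20 points, which is the whole effect the trial is designed to detect.

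**The case against.** The strongest reply is that the operative parts of the article are already comparative. Hypothesis 1, the Power calculation and the opening of the Discussion all concern sessions against the book. The clause on 12–14 sessions appears once, in the description of the interventions, and no aim, hypothesis, outcome or analysis depends on it. The control was chosen openly, for stated scientific and ethical reasons. All of this stands, and it is why the remedy is wording and not design. It does not rescue the clause or the efficiency claims, which say in plain terms what the trial will show.

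A second reply is that if sessions beat the book, and the book does no harm, face-to-face CRAFT must beat nothing. That inference rests on an assumption (the Power calculation asserts that CRAFT cannot make matters worse), gives no size against no CRAFT, and leaves self-help alone untested.

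On the third statement, a reader might infer that the protocol intends to treat a failed superiority test as equivalence and to roll out the book on that basis. The documents do not support this. The sentence beginning "If the self-help material proves to be just as effective as other types of intervention" is a conditional remark with no test or decision rule attached, and a trial with superiority hypotheses owes no margin. Nor does any section plan to present within-arm entry rates as proof that CRAFT works. One-sidedness is stated for the sample size only; the Statistical analyses section does not fix it for the tests.

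**Conclusion.** Two promised conclusions are wrong as written. The design cannot test six sessions against 12–14, and its randomized comparison cannot show that CRAFT, self-help included, is efficient in Denmark. This follows from the arms themselves and needs no assumption. The choice of control is not at fault, and the comparison between formats is unaffected.

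The secondary point is a caution about interpretation. On the assumptions of 8 clinics and about 108 analysed per arm with ICC 0.05, an estimate near zero would carry an interval of roughly ±17 points for one arm against the book, or ±14 if the face-to-face arms are pooled. Such a result would be compatible with a sizeable advantage for sessions. Non-significance is fairly unlikely if the true difference is the planned 20 points (about 25%), but probable if it is 10 points (about 69%); both figures are for a single arm against the book. That a null result would be taken as equivalence is a risk, not something the protocol states.

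**What to change.** 1. In Individual and group sessions, delete the claim to test six against 12–14 sessions, or label it an external, non-randomized comparison.
2. Restate Aim 2 (Abstract, and Aim and hypotheses), the Abstract's Discussion and the last paragraph of the main Discussion as the effect of individual or group CRAFT relative to self-directed CRAFT. State that treatment-entry rates within an arm are descriptive only.
3. Beside the Discussion's remark on self-help, state that a non-significant difference will be reported with its confidence interval as inconclusive, not as equivalence. If a claim of similar effect is really wanted, it needs its own hypothesis, a margin justified in advance and a sample size to match.

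Items 1 and 2, and the reporting statement in item 3, change wording only; arms, recruitment and data collection stay as they are. The price is that the trial claims less.

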**Fig. 2 Fig2:**

Project time-line

The group CRAFT and the individual CRAFT interventions cover the following topics [8]:Training in recognition of early signs of domestic violence, particularly as new behavioural change techniques are introduced, intentionally designed to be experienced as negative by the PWAUD; development of a safety plan.Development of a functional analysis to outline the triggers of the drinking problem, as well as the positive and negative consequences of it; training in identifying the CSO’s own unintentional role in the maintenance of the PWAUD’s using cycle.Training in effective communication with the PWAUD. Training in appropriate and consistent use of positive reinforcement of the PWAUD’s non-using prosocial behaviour.Training in positive reinforcement. Learning to reinforce clean and sober behaviour by using small rewards.Training the withdrawal of reinforcement at times of drinking episodes in order to allow for the natural negative consequences of PWAUDs’ using behaviour.Help to identify the CSO’s own areas of life dissatisfaction and training the development of specific plans for addressing that dissatisfaction and in rewarding themselves more often.Training the methods on how and when to suggest treatment to a PWAUD. Development of a “rapid intake” plan. Working with how to handle disappointments in a fruitful way.

##### Self-directed CRAFT format (control)

CSOs, randomized to the control condition, will receive the self-help material, only, and are considered controls for the first three months after enrollment. The self-help material is a Danish book [31], inspired by the American CRAFT self-help book “Get Your Loved One Sober” [32] and the German self-help book “Strategien zur Selbsthilfe für Angehörige von Menschen mit Alkoholproblemen, Der Community Reinforcement Ansatz: das Familien-Training (CRAFT)” [33]. In addition, we added a chapter about what alcohol dependence is like, in addition to describing alcohol treatment, how it is organized and how it can be sought. The CRAFT studies, so far, indicate that the effect of the face-to-face intervention is mainly seen either during the intervention or shortly after completion of the intervention. In other words: empowering the CSOs seems to lead to rather immediate changes in relation to treatment-seeking behaviour among PWAUD.

Since we expect a higher impact from the face-to-face intervention than from the control condition, all participants in the control condition have the option for a face-to-face session with therapist three months after enrollment in the study, in order to ensure that the participants are feeling sufficiently helped. The additional face-to face session for the control group is for ethical reasons and postponed in time, in order not to disturb the testing of the interventions.

#### Participating therapist and training

The therapists delivering the CRAFT intervention will be staff from the participating treatment centers. Typically, the therapists are educated nurses or social workers with extensive experience in the treatment of alcohol abuse disorders. Therapists from the participating centers, randomized to deliver either group-based or individual CRAFT, have received three days free training in CRAFT, funded by the present project. To avoid disappointment if a participating center is randomized to deliver self-directed CRAFT, the control intervention, and in order to add to the overall implementation of CRAFT nationwide, therapists will be offered identical training free of charge when the enrollment of participants is completed.

During the study, all therapists, delivering the experimental intervention, will receive feedback on recordings of their intervention performance. All face-to-face intervention sessions will be recorded, and feedback will be given on randomly picked recordings.

#### Instruments and data collection

Data will be collected at baseline (t0), three months (t1), and six months (t2) by means of an iPad (baseline) and by a Web-based battery of questionnaires or by telephone interview (at follow-ups). The participants receive up to three reminders for the follow-up questionnaire until they have answered. Data on whether and when PWAUD start treatment, will be collected from the CSO after three and six months after completion of enrollment of CSOs.

The questionnaire will consist of the following instruments (Table 1):

**Table 1 Tab1:** Instruments at baseline, first follow-up and second follow-up

	Baseline	First follow-up after 3 months from baseline (t_1_)	Second follow-up after 6 months from baseline (t_2_)
Instruments			
Demographic information	X		
Information on whether the drinker has sought treatment (primary outcome)		X	X
Audit about use of Alcohol [34]	X	X	X
Quality of life [35]	X	X	X
Self-reported number of days with sick leave within the last 30 days	X	X	X
Time spent with the problems drinker [36]	X	X	X
The drinker’s use of alcohol (according to the CSO) [36]	X	X	X
PHQ9_Danish [37]	X	X	X
Coping Questionnaire 30 items form [38]	X	X	X
Family Member Impact Questionnaire [38]	X	X	X
Personal Happiness Scale [39]	X	X	X
Satisfaction with the intervention received [40]		X	X

### Outcome measures

#### Primary outcome

The primary outcome is the proportion of drinkers, who enter alcohol treatment from baseline and until three months after their CSOs’ enrollment in the CRAFT study.

#### Secondary outcomes

Changes in the anxiety and depression symptoms of CSOs following CRAFT interventionImprovement in the relationship between the CSO and PWAUD before and after CRAFT interventionSelf-reported changes in number of sick leave days for CSOs from 6 months before to 6 months after enrollment in the studyChanges in quality of life among CSOs

### Statistical analyses

Data will be analyzed using a mixed effect logistic regression model, mixed effects Poisson regression, and univariate statistical models, including t-tests, and chi2-tests, will be used for descriptive statistics. For some of the quantitative secondary outcomes a mixed effect model (for normally distributed data) or a random effect quantile regression model will be used. Strategy for missing data will be based on multiple imputations with special emphasis on the sensitivity of the results of various imputation schemes, as the missing mechanism is likely to be missing not at random.

### Ethics

In view of the fact that the CRAFT intervention has proven highly effective in the US, and since living close to a problem drinker is such a burden to the individual and, finally, because the Danish National Guidelines strongly recommend the implementation of CRAFT, we find it un-ethical and problematical not to offer CRAFT in some form to all the participants, even to the control condition. However, since we expect less effect of the control condition (CRAFT as self-help material), for ethical reasons, the participants in the control group will be offered an individual CRAFT session three month after enrollment. Training significant others in new communication strategies and new ways of acting, in relation to the problem drinker, may lead to increased tension in the family set-up. Domestic violence is already relatively more frequent in families with problem drinking, thus, an increased risk may be anticipated. It is, therefore, highly important to address the risk of domestic violence in therapy. Addressing this risk is mandatory in the interventions and includes developing safety plans together with the CSO. It is, however, important to bear in mind that the risk of abuse and suffering, on the part of the CSOs, is even higher if the problem drinking continues unaddressed. We expect no risks or side-effects for the participants.

